#### Pre- and post-program quantitative cross-sectional community surveys

The community-based evaluation component will assess whether the I-TREC program has an impact on blood pressure and blood glucose awareness, treatment seeking, and control among adults in the community. This evaluation component is critical to learning the real-world impact of the I-TREC program on community-level indicators of the care continuum (screening, treatment, control). Data collected in the program and comparison blocks prior to the program will be compared with data collected from these same blocks after the program using identical procedures. This design allows us to assess and address several threats to validity, including lack of temporal order, comparability across the two blocks (leading to potential confounding by population composition) and secular changes unrelated to our program that affect study endpoints (leading to potential confounding by external factors). Given that we will be sampling separate cross-sections of the population in each group and time point, we do not expect inference to be affected by population aging (maturation threats) over the 3-year program period.

At baseline—prior to intervention—we employed a multi-stage cluster sampling design to obtain a representative sample of adults aged 30 years and older in both blocks under study. Within each block, census data were used to select villages proportionate to population size and subsequently we conducted household mapping and listing to generate a sampling frame for households. Households were selected using systematic random sampling, and one adult man and woman from each household were randomly selected using the Kish method to achieve the desired sample size. At endline, this same procedure will be repeated.

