The community survey sample size was determined to estimate differences in mean reduction in systolic blood pressure among those with diagnosed hypertension in the community. First, we computed the base sample size required to detect a desired effect size of 5 mmHg given the SBP standard deviation of 18.5, power = .80 and α = .05, based on the mPower Heart Study [24]. We estimated that 168 individuals with hypertension would be needed to detect the anticipated effect size. Second, we estimated that we would require a sample size of 839 adults in the general population to identify 168 individuals with hypertension, assuming prevalence of diagnosed hypertension of 20%. Third, we determined the optimal sample allocation for a multi-stage sampling design that would be time-efficient for field work and statistical precision. We assumed an intraclass correlation of systolic blood pressure of 0.018 based on village-level clustering of SBP in the DISHA study [32] (unpublished findings). After applying a 10% refusal rate based on our prior field studies in the region, we determined that a cluster size of 50 adults per village distributed across 35 villages per block was optimal. This yielded a total sample size of 3508 for the community survey to be evenly split between the program and comparison blocks.

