The coefficient associated with the interaction term, “program group x pre-post indicator,” is the adjusted DiD estimate accounting for heterogeneity in socio-demographic characteristics. The model will be estimated using generalized estimating equations (GEE) to account for clustering of outcomes within the villages (i.e. village is the cluster variable specified for statistical analysis). Sub-group analyses will examine differences by gender and socioeconomic status.

Data points recorded in the I-TREC system will be analyzed by month to examine trends over time and seasonality. We will also evaluate change patient outcomes over time (e.g., mean SBP change). While several of the I-TREC platform indicators are purely descriptive measures of performance (e.g., mean time for data upload), other indicators of healthcare delivery may be compared between I-TREC facilities and comparison group facilities (e.g., patient volume).

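### The community survey is sized with a two-group variance but analysed as a difference-in-difference over four separate samples, so the stated 80% power for 5 mmHg is not delivered

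*Protocol article*

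**What the plan says.** The sample-size paragraph, under the heading on pre- and post-program community surveys, gives its target: "The community survey sample size was determined to estimate differences in mean reduction in systolic blood pressure among those with diagnosed hypertension". Its inputs are a "desired effect size of 5 mmHg given the SBP standard deviation of 18.5", with "power = .80 and α = .05"; whether alpha is one- or two-sided is not stated. The result is: "We estimated that 168 individuals with hypertension would be needed to detect the anticipated effect size". The chain then runs through 839 adults at 20% diagnosed prevalence, an intraclass correlation of 0.018, 10% refusal, and 50 adults in each of 35 villages per block. It ends: "This yielded a total sample size of 3508 for the community survey to be evenly split between the program and comparison blocks".

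The same section explains why population aging is not expected to affect inference: "Given that we will be sampling separate cross-sections of the population in each group and time point". It adds that the baseline procedure will be repeated at endline. The statistical analysis plan section fits a model with a group-by-time interaction, clustered by village, and says that the interaction coefficient "is the adjusted DiD estimate accounting for heterogeneity in socio-demographic characteristics".

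**The concern.** A difference between blocks in mean reduction is a difference-in-difference (DiD). When each block and round is a separate sample, nobody contributes a within-person change. The estimate is built from four independent means, and no pre-post correlation is available to reduce its variance. A formula for two means therefore understates that variance by a factor of two.

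The Summary section of the article acknowledges that the comparison block has no patient data comparable with the eCRF, and looks to the community survey to supply the controlled comparison. This is also the only controlled contrast for which a sample size is given. If the stated power is too high, an inconclusive endline result would be read against a sensitivity the survey does not have.

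**Working it through.** **Inputs** (all from the sample-size paragraph): effect 5 mmHg; SD of SBP 18.5; power 0.80 (z = 0.8416); alpha .05 (z = 1.960 two-sided, 1.645 one-sided); prevalence 20%; ICC 0.018; refusal 10%; 50 adults x 35 villages per block. The total of 3508 is read as applying to each round, because the procedure is repeated at endline.

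**1. Reproduce the plan's chain.**
- 168 / 0.20 = 840 (stated 839; 839 x 0.20 = 167.8).
- Design effect = 1 + (50 − 1) x 0.018 = 1.882.
- 839 x 1.882 / 0.9 = 1754.4 per block; x 2 = 3508.9 (stated 3508).

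The chain closes only if 168 is the effective number with hypertension per block.

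**2. Which formula gives 168?**
- Two means, n per group = 2 x (z_α + z_β)² x 18.5² / 5²: 169.3 one-sided, 214.9 two-sided.
- DiD over four independent cells, n per cell = 4 x (z_α + z_β)² x 18.5² / 5²: 338.6 one-sided, 429.8 two-sided.

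The stated 168 is close to the one-sided two-group figure and far from either DiD figure.

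**3. Separate the effect of sidedness.** With 168 per group and no DiD, SE = 18.5 x √(2/168) = 2.02. Power is 80% one-sided and 70% two-sided.

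**4. DiD power for 5 mmHg.** SE = 18.5 x √(4/n_eff); power = Φ(5/SE − z_α); detectable effect at 80% = SE x (z_α + 0.8416).

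| Basis | n_eff per cell | SE | Power, one-sided | Power, two-sided | Detectable, two-sided |
|---|---|---|---|---|---|
| A. Plan's design effect, 1.882 | 168 | 2.855 | 54% | 42% | 8.0 mmHg |
| B. Design effect on about 9 people with hypertension per village | 276 | 2.228 | 73% | 61% | 6.2 mmHg |
| C. As B, no loss from the inflated sample | 301 | 2.132 | 76% | 65% | 6.0 mmHg |
| D. Same villages, fully persistent village effects | 321 | 2.066 | 78% | 68% | 5.8 mmHg |
| E. As D, no loss from the inflated sample | 356 | 1.960 | 82% | 72% | 5.5 mmHg |

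- Row B: 1754.4 x 0.9 x 0.20 = 315.8 with hypertension per cell; 315.8 / 35 = 9.02 per village; design effect 1 + 8.02 x 0.018 = 1.144; 315.8 / 1.144 = 276.
- Row C: 350 per cell, 10 per village; design effect 1 + 9 x 0.018 = 1.162; 350 / 1.162 = 301.
- Rows D and E: the village component cancels, leaving within-village variance; 315 / (1 − 0.018) = 321 and 350 / 0.982 = 356.

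Rows C to E rest on assumptions that the article does not state.

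**The case against.** The strongest reply has four parts.

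- **Sidedness.** A reader might infer that the doubled variance alone takes power from 80% to 42%. The documents do not support that. Sidedness is unstated and 168 comes close only one-sided, so about 10 points of that fall (80% to 70%) come from moving to a two-sided test. Like for like, one-sided and with the plan's design effect, the DiD takes power from 80% to 54%.
- **Slack in the design effect.** The plan inflates for 50 adults per village, although only about 9 of them would be in the analysis of people with diagnosed hypertension. On the smaller design effect, a simple two-group comparison would have 89% power two-sided or 94% one-sided. This slack offsets part of the DiD penalty. It also means that rows A and B rest on different clustering models and should not be quoted as one range without saying so.
- **Retained villages.** The article does not say whether the baseline villages are sampled again. If they are, and village effects persist fully, one-sided power is about 78%, or 82% with no loss from the inflated sample.
- **Another route to 168.** A two-sided change-score formula with pre-post correlation 1 − 168/429.8 = 0.61 also gives 168. That would be a different mistake, and it too is incompatible with separate cross-sections.

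The first three stand as qualifications of the size. None removes the defect: recovering 80% takes one-sided testing, the smaller design effect, retained villages with fully persistent effects and no loss, all at once. The article does not state that combination.

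A reader might also infer that the DiD estimate is invalid or that enrolment must grow. Neither follows. The estimate and its interval remain valid; the power statement is what is wrong.

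**Conclusion.** The point holds in qualified form. The sizing omits the variance of a DiD over four separate samples, and the article's own chain shows this without reference to any outside document. A flat claim of 42–61% power would go too far, because it fixes a two-sided test that the article does not specify and mixes two design effects.

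The supportable statement has two parts: 54% one-sided or 42% two-sided on the plan's design effect, and 73% or 61% on a design effect for about 9 people with hypertension per village. On the stated inputs and a two-sided test, the detectable DiD is about 6.2 to 8.0 mmHg across those two bases, against the 5 mmHg claimed.

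These figures assume 20% diagnosed prevalence, ICC 0.018, SD 18.5, 3508 adults per round and no variance reduction from covariates. If 3508 covered both rounds together, power would be lower still: 877 x 0.2 x 0.9 = 157.9 per cell; divided by 1 + 3.5 x 0.018 = 1.063, this leaves 148.5 effective, and power is about 50% one-sided or 38% two-sided.

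**What to change.** In the sample-size paragraph, replace the two-group formula with the DiD variance, 4 x SD² x design effect / n per cell. State whether alpha is one- or two-sided, which cluster size the design effect uses, and whether the baseline villages are retained at endline.

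The Current status section reports that the baseline survey is complete. So, before endline fieldwork, restate either the power for 5 mmHg or the detectable DiD for the planned 3508 per round. Base it on the SD, the village ICC and the number of people with diagnosed hypertension actually observed at baseline. The figures above should not be inserted as they stand, since they depend on choices that are the investigators' to declare.

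The cost is a rewritten paragraph, a short calculation on data already held, and a less favourable stated figure. Enrolment, procedures and the analysis model are unchanged.

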## Background

Hypertension and diabetes together affect over 275 million Indians and their families [1]. These conditions are rising rapidly in all regions of India, commonly co-occur [2–4], and are associated with several adverse health outcomes—such as higher rates of death, myocardial infarction, stroke, blindness, kidney failure. Yet, both hypertension and diabetes are treatable such that timely and appropriate therapy mitigates associated morbidity due to complications and premature mortality. While lack of diagnosis is among the major obstacles to seeking appropriate treatment [5, 6], treatment outcomes even after diagnosis are far from ideal. Less than half of individuals who have hypertension and diabetes in the community are aware of their condition [7, 8], and only 20–25% achieve adequate blood pressure [9] or blood glucose control [10]. Under-diagnosis, under-treatment, and poor control for both hypertension and diabetes are disproportionately high in rural settings [11, 12], where the majority of the Indian population resides.

India’s rural healthcare system is currently organized as a hierarchy of facilities that range from relatively lower-skilled personnel supported by simple infrastructure at the village level to relatively higher-skilled personnel supported by sophisticated infrastructure at the district level. This model attempts to maximize geographical coverage by allowing for “up referrals” and “down referrals” across levels of the healthcare system so that the demand of the individual patient can be met by appropriate resources, such as skilled human resources, infrastructure and services. The referral linkages between these institutions, while theoretically in place, are not implemented efficiently or cohesively. In practice, patients access any level of the healthcare system convenient for them, resulting in a mismatch between patient needs and resource availability. Challenges to the system are compounded by the heterogeneity of treatment guidelines, diagnostic modalities, and medications [13–17] needed at all levels of health care to appropriately serve the growing population with NCDs alongside the large population seeking care for maternal and child health and infectious diseases [18–21].

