#### Outcomes

Program indicators are guided by the Reach, Effectiveness, Adoption Implementation, and Maintenance (RE-AIM) framework [31]. The principal endpoints for evaluation are shown in Table 2, and focus on the domains of reach, effectiveness, adoption, and implementation of the program components. Reach and effectiveness will be assessed using a combination of community-based data and facility-based data. For example, the proportion of adults ages 30 and older in the community who are screened for hypertension is a measure of reach that will be obtained through a representative community survey. A second measure of reach is the number of patients seeking care for hypertension and diabetes who have an eCRF, which will be measured through health facility data. Similarly, effectiveness will be assessed through health outcomes (e.g., reductions in mean blood pressure and/or mean blood glucose) among patients attending program facilities and also among adults with hypertension and/or diabetes in the community. Adoption metrics focus on healthcare provider utilization of the eCRF and CDSS tools. Implementation measures focus on quantifying the proportion of patients who receive care through the eCRF and CDSS tools. Finally, maintenance will be assessed through qualitative research with stakeholders within the health system to understand views of sustainability.

**Table 2 Tab2:** Key outcome indicators for the I-TREC evaluation

RE-AIM domain	Key indicators
**Reach**	Proportion of adults ages 30 and older in the community screened for hypertension by a government healthcare provider
	Proportion of adults ages 30 and older in the community screened for diabetes by a government healthcare provider
	Number of patients seeking care for hypertension and diabetes at a government health facility who have an eCRF
**Effectiveness**	Reduction in mean blood pressure in patients receiving care in program facilities
	Reduction in mean blood glucose in patients receiving care in program facilities
	Proportion who achieve blood pressure and blood glucose control among patients receiving care in program facilities
	Proportion who achieve blood glucose control among patients receiving care in program facilities
	Reduction in mean blood pressure in the community
	Reduction in mean blood glucose in the community
	Proportion of hypertension patients who achieve blood pressure control in the community

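### The community survey is sized on SBP in people with diagnosed hypertension, which disagrees with the listed outcome populations and is a group the program itself can change

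*Protocol article*

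**What the plan says.** The sample-size paragraph (community surveys section) sets out to "estimate differences in mean reduction in systolic blood pressure among those with diagnosed hypertension in the community". It aims to "detect a desired effect size of 5 mmHg given the SBP standard deviation of 18.5, power = .80 and α = .05", and reaches the general-population sample by "assuming prevalence of diagnosed hypertension of 20" percent.

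Other places name other populations:
- Table 2 lists "Reduction in mean blood pressure in the community", with no restriction to diagnosed people.
- The Outcomes text says effectiveness will be assessed in facility patients and "also among adults with hypertension and/or diabetes in the community", without saying whether those adults must be diagnosed.
- The statistical analysis section speaks of mean blood pressure in the community surveys.
- The sample-size paragraph itself drops the word diagnosed one step later: "We estimated that 168 individuals with hypertension would be needed to detect the anticipated effect size".

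Three features of the plan bear on this. Table 1 makes community screening and confirmatory diagnosis tasks of the program, and the community survey is meant to test its effect on awareness. Each wave samples a fresh cross-section. The DiD model adjusts for age, sex, education, religion, marital status, poverty status and facility type.

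**The concern.** The populations named are different estimands, and the only one tied to the 5 mmHg target is defined by a status that the program is meant to alter. If screening finds more cases in the program block, the diagnosed group there at endline includes people who would not have counted at baseline. DiD removes stable differences between blocks and trends common to both. It does not remove a program-induced change in who belongs to the analysed group, and sociodemographic covariates do not stand in for time since diagnosis.

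A program that only diagnosed more people, with no effect on anyone's blood pressure, could then show a non-zero DiD. If the newly found cases are milder, the bias looks like benefit. If they have higher SBP because they are untreated, it hides benefit or looks like harm. The same holds for the proportion controlled if its denominator is diagnosed people. The community survey is the article's main protection against the lack of comparison-block patient data, so this contrast carries much of the weight.

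**Working it through.** **1. The plan's own sample size.** Inputs, all from the sample-size paragraph: difference 5 mmHg, SD 18.5, power 0.80, α 0.05, diagnosed prevalence 20%, intraclass correlation 0.018, 50 adults per village, 10% refusal.
- Two-group formula, n per group = 2 × [18.5 × (z_α + z_0.80) / 5]². One-sided this gives 169.3, close to the stated 168. Two-sided it gives 214.9, which does not match. Sidedness is a separate matter.
- 168 / 0.20 = 840 (stated 839; 839 × 0.20 = 167.8).
- Design effect = 1 + 49 × 0.018 = 1.882.
- 839 × 1.882 / 0.90 = 1754.4 per block; × 2 = 3508.9 (stated 3508).

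The chain reproduces, which confirms that the survey is sized on diagnosed people at one fixed prevalence of 20%. No endline or block-specific prevalence is given.

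**2. Case-mix shift with no treatment effect.** Let p be the endline diagnosed prevalence in a block, starting from 20%. The share of the endline diagnosed group added since baseline is f = (p − 0.20) / p. Let d be the SBP gap between newly and previously diagnosed people, taken as equal in both blocks. Then

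shift in DiD = (f_program − f_comparison) × d.

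Both p and d are assumptions, because the article gives neither.

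| Endline diagnosed, program vs comparison | f_program − f_comparison | Shift, d = 5 mmHg | Shift, d = 10 mmHg |
|---|---|---|---|
| 30% vs 30% | 0.333 − 0.333 = 0 | 0 | 0 |
| 22% vs 20% | 0.091 − 0 = 0.091 | 0.45 | 0.91 |
| 25% vs 22% | 0.200 − 0.091 = 0.109 | 0.55 | 1.09 |
| 30% vs 25% | 0.333 − 0.200 = 0.133 | 0.67 | 1.33 |
| 30% vs 20% | 0.333 − 0 = 0.333 | 1.67 | 3.33 |

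The sign follows the sign of d. As shares of the 5 mmHg target, the 25% vs 22% row is 11-22% (0.55/5 to 1.09/5) and the last row 33-67% (1.67/5 to 3.33/5). A spurious 5 mmHg would need d = 15 at 30% vs 20%, or d = 25 at 25% vs 20%.

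**3. Is there room for such rises?** The Background states: "Less than half of individuals who have hypertension and diabetes in the community are aware of their condition". If 20% are diagnosed and under half of cases are aware, total prevalence exceeds 0.20 / 0.5 = 40%, so more than 20% of adults would be undiagnosed. Reaching 30% would need at most half of them found. The awareness figure is a general one for India, not a baseline measurement in these blocks, so this shows only that the scenarios are possible.

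**The case against.** The strongest reply is that the article does not fix a diagnosed-only analysis. That restriction is explicit only in the sample-size paragraph; the outcome and analysis sections are wider. A reader might infer that diagnosed-only SBP is the planned effectiveness comparison, and the documents do not support that. What they show is a disagreement between the sized population and the listed ones. This part of the objection stands.

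Second, the contrast between blocks may be small. Screening adults aged 30 and over is national policy (Background), providers in both blocks receive the same content training (Healthcare provider training), the comparison block is described as lacking electronic records and decision support rather than screening (Routine care), and the pandemic closed lower-tier facilities (Current status). This also stands: a rise in the program block alone is the extreme case, and equal rises give no bias.

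Third, much of the remedy is arguably present already. Table 2's community mean reads naturally as all surveyed adults, and awareness is already something the survey evaluates. That makes the repair easy, but leaves the 5 mmHg target attached to the one population that the program can change.

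It could also be said that a working definition of hypertension belongs in the full protocol or the analysis plan. A condensed article may leave such detail out, but this one names populations that conflict.

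**Conclusion.** The point holds as an inconsistency with a bias risk attached. The sized population and the listed outcome populations disagree, and following the sized one would condition on a status affected by the program, with nothing in the stated model to correct for it.

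The size rests entirely on assumed values. For a gap of 5-10 mmHg it runs from zero with equal rises, through about 0.5-1.1 mmHg at 25% vs 22%, to 1.7-3.3 mmHg with a rise to 30% in the program block only. The calculation also assumes 20% diagnosed in both blocks at baseline, the same gap in both, and no change among those already diagnosed. A reader might infer that a bias of several mmHg has been shown. It has not: a 3 mmHg shift needs a clear difference between blocks together with a gap of about 9 mmHg (30% vs 20%) or 15 mmHg (25% vs 20%). Even 1 mmHg is a fifth of the target, though, and its direction cannot be known beforehand. This should be settled before the endline analysis.

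**What to change.** Reconcile the sample-size paragraph with the Outcomes text, Table 2 and the analysis section, and then state:
- Mean SBP in all surveyed adults aged 30 and over is the selection-free community comparison.
- For mean SBP among people with hypertension, and for the control denominator, one definition applies in both waves and does not require prior diagnosis: survey blood pressure of at least 140/90 (the article's own screening threshold, used here only to define the analysis group) or current antihypertensive medication. An equivalent rule applies for diabetes.
- Diagnosed-only SBP is secondary, reported beside the change in diagnosed prevalence in each block.

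The cost is analysis wording, provided blood pressure is measured in all survey participants. Table 2 and the analysis section imply this, but the survey procedures are not described.

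There are two downsides. The effect is diluted in the wider groups: if a 5 mmHg effect were confined to the 20% diagnosed, the all-adult mean would move by 0.20 × 5 = 1 mmHg. The target should therefore be restated, and power checked, for the chosen population. Also, the pressure-or-medication definition is less sensitive to awareness but not untouched by the program. It depends on treatment, which follows diagnosis, and it partly conditions on the outcome, since people controlled without medication leave the group. For that reason the all-adult mean has to carry the selection-free comparison.

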#### Health outcomes among patients receiving the I-TREC program

Using patient health data from the eCRF, we will assess processes of care and changes in blood pressure and blood glucose outcomes over time among patients with hypertension or diabetes who seek care at I-TREC program facilities in a facility-based evaluation component. Because I-TREC is being integrated into the routine care in the program block under real-world conditions, we will not be assigning individual patients to treatment nor actively following patients for research visits. Rather, all adults residing in the I-TREC catchment area (i.e., residents of Mukandpur block) will be exposed to the program and patient data will be collected every time a person chooses to receive care at a government health facility. Data from all patients visiting facilities in the program block captured in the Government of India eCRF will be de-identified and obtained by AIIMS throughout the program period for monitoring and evaluation purposes.

The sample size for the facility-based evaluation is out of our control and contingent on the number of patients who seek care at government facilities. We therefore report the detectable effect size for longitudinal change in systolic blood pressure over time in patients at I-TREC facilities after setting power to 80% and α = .05. The program block, Mukandpur, has a population of 98,000. We expect that 30% of the local population will seek care at a government facility, 50% will be age-eligible (30 years and older) per the government guidelines for universal and opportunistic screening of hypertension and diabetes, and 20% will test positive for hypertension, amounting to an estimated patient pool of 2940 adults. Assuming that 50% of all enrolled patients with hypertension and diabetes make repeat visits (enabling us examine changes in outcomes), we will be able to detect a 1.35 mmHg difference in SBP.

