#### Statistical analysis plan

Quantitative data analysis will be performed using SAS, STATA, and R software. Descriptive analyses of the community-based data will examine socio-demographic characteristics, health indicators, and healthcare behaviors of the program and comparison block samples at baseline and end-line. The quantitative evaluation of health and healthcare endpoints will focus on assessing changes in the continuum of care indicators and mean blood pressure in the community-based surveys. We will assess changes in baseline to end-line indicators of health outcomes (e.g., blood pressure) and changes in continuum of care indicators (e.g., proportion screened) for both the program and comparison blocks; see Table 2 for indicators. A simple difference-in-difference (DiD) [33] estimate for each indicator will be computed as
$$ \mathrm{DiD}=\left({p}_{g=\mathrm{i},\mathrm{t}=1}-{p}_{g=\mathrm{i},\mathrm{t}=0}\right)-\left({p}_{g=\mathrm{c},\mathrm{t}=1}-{p}_{g=\mathrm{c},\mathrm{t}=0}\right) $$where p indicates prevalence or mean of each indicator; *g* subscripts group (i = program; c = comparison); and t subscripts the time point of data (0 = pre-program; 1 = post-program). We will estimate log-binomial models (binary outcomes) or linear models (continuous outcomes, with log-transformation if needed) with robust variance to compute the DiD after accounting for compositional characteristics of the community and clustering of data within villages. For each outcome indicator separately, the following model will be estimated using individual-level data:
$$ \mathrm{Outcome}\ \mathrm{indicator}\sim \mathrm{program}\ \mathrm{group}+\mathrm{pre}-\mathrm{post}\ \mathrm{indicator}+\mathrm{program}\ \mathrm{group}\ \mathrm{x}\ \mathrm{pre}-\mathrm{post}\ \mathrm{indicator}+\mathrm{age}+\mathrm{sex}+\mathrm{education}+\mathrm{religion}+\mathrm{marital}\ \mathrm{status}+\mathrm{below}\ \mathrm{poverty}\ \mathrm{line}+\mathrm{facility}\ \mathrm{type}\ \left(\mathrm{public}\ \mathrm{versus}\ \mathrm{private}\right). $$

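### The stated 80% power for 5 mmHg fits a two-group comparison at one time point; the planned difference-in-difference has about 61% (two-sided)

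*Protocol article*

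**What the plan says.** All references are to the protocol article.

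- **Target.** The section on the pre- and post-program community surveys states: "The community survey sample size was determined to estimate differences in mean reduction in systolic blood pressure among those with diagnosed hypertension in the community".
- **Inputs.** It takes a "desired effect size of 5 mmHg" "given the SBP standard deviation of 18.5, power = .80 and α = .05". Sidedness is not given.
- **Result.** "We estimated that 168 individuals with hypertension would be needed to detect the anticipated effect size". At 20% prevalence of diagnosed hypertension this becomes 839 adults. With an intraclass correlation (ICC) of 0.018, 50 adults per village, 35 villages per block and 10% refusal, the section arrives at a "total sample size of 3508 for the community survey to be evenly split between the program and comparison blocks".
- **Sampling.** The same section says that each group and time point is a separate cross-section, and of the second round: "At endline, this same procedure will be repeated".
- **Analysis.** The Statistical analysis plan section states: "A simple difference-in-difference (DiD) [33] estimate for each indicator will be computed as". The formula that follows is the pre-post change in the program block minus that in the comparison block. The adjusted estimate is the group-by-period interaction from a GEE model clustered on village.

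**The concern.** The quantity named in the sample-size paragraph, a between-block difference in mean reduction, is a difference-in-difference, and the analysis section estimates exactly that. With four independent samples, each of the four means contributes its own sampling variance. A sample size built on two means understates what is needed by a factor of two.

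The community survey is the evaluation's only controlled comparison of health outcomes. The article's Summary says that the comparison block has no patient data comparable to the eCRF. If the survey is believed to have 80% power at 5 mmHg when it has materially less, an inconclusive result could be taken as evidence that the program does not lower blood pressure.

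**Working it through.** **Inputs from the article:** difference 5 mmHg; SD 18.5 (variance 342.25); power 0.80 (z = 0.842); alpha 0.05 (z = 1.960 two-sided, 1.645 one-sided); ICC 0.018; prevalence 20%; refusal 10%; 50 adults in each of 35 villages per block.

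**Step 1: what the 168 counts.**
- 839 × 0.20 = 167.8, so 839 adults yield 168 hypertensives.
- Implied design effect: 1 + (50 − 1) × 0.018 = 1.882.
- 839 × 1.882 / 0.9 = 1754.4 per block; × 2 = 3508.9, stated as 3508.

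The chain closes only if 168 is per block. Since the procedure is repeated at endline, it is per block per round.

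**Step 2: which formula gives 168.** For two means at one time point, n per group = 2 × (z_alpha + z_power)² × SD² / difference².
- One-sided: 2 × (1.645 + 0.842)² × 342.25 / 25 = 169.3 (168.4 with z values rounded to 1.64 and 0.84).
- Two-sided: 2 × (1.960 + 0.842)² × 342.25 / 25 = 214.9, so 215.

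The one-sided version comes close to 168. The two-sided version does not: 168 per group gives it 69.7% power.

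**Step 3: what the planned estimator needs.** For four independent samples of effective size n, variance = 4 × SD² / n, against 2 × SD² / n for two samples. The requirement per cell (one block in one round) is 4 × (z_alpha + z_power)² × SD² / difference²:
- Two-sided: 4 × 7.849 × 342.25 / 25 = 429.8, so 430 effective hypertensives.
- One-sided: about 339.

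**Step 4: what the planned sample provides.**
- Hypertensives per cell: 1754 × 0.9 × 0.20 = 315.7, about 316.
- Per village: 316 / 35, about 9.
- Design effect for the subgroup analysed: 1 + (9 − 1) × 0.018 = 1.144.
- Effective n: 315.7 / 1.144 = 276.

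**Step 5: power at 5 mmHg.** SE = 18.5 × √(4/n); power = Φ(5/SE − z_alpha); detectable difference = 2.802 × SE (two-sided, 80% power).

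| Effective n per cell | SE | Two-sided power | One-sided power | Detectable difference |
|---|---|---|---|---|
| 276 (design effect 1.144) | 2.23 | 61% | 73% | 6.2 mmHg |
| 168 (design effect 1.882) | 2.86 | 42% | 54% | 8.0 mmHg |
| 316 (no clustering) | 2.08 | 67% | 78% | 5.8 mmHg |

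The second row applies the design effect for all 50 adults per village to an analysis that uses about 9 of them, so it is a conservative lower bound. The third row ignores clustering and is an optimistic limit. Neither it nor the first row reaches 80%, on either sidedness. One-sided testing with neither clustering nor refusal would just reach it (81%), but the article assumes both.

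**Step 6: sidedness elsewhere in the article.** The facility-based calculation expects 2940 patients, half with repeat visits, so 1470. If the same SD of 18.5 is used (an assumption, since that paragraph gives none), 2.802 × 18.5 / √1470 = 1.35 mmHg, the stated figure. One-sided alpha would give 1.20. The two calculations in the article therefore appear to use different sidedness.

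**The case against.** **Sidedness and unit are inferred.** The article gives no formula, and the one-sided result is 169.3, not exactly 168. This stands, so the one-sided origin should be called apparent. The shortfall does not depend on it: one-sided power for the planned estimator is about 73%. The per-block reading rests on a chain that closes to within one person.

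**The design effect is generous.** The plan inflates for 50 adults per village when only about 9 enter the analysis. This is correct, and the 61% already credits it. The 276 effective hypertensives would suffice for a two-sided comparison at endline alone (about 89% power), but that is not the planned analysis.

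**Covariates reduce residual variance.** The model adjusts for age, sex, education and other factors. If they explained 10–15% of SBP variance (an assumption), two-sided power would be 66–68%. Reaching 80% needs a residual SD of about 14.8, or 1 − (14.8/18.5)² = 36% of variance explained. The article gives no basis for that.

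**A pre-post correlation could justify 168.** In a panel, a correlation of about 0.61 would make 168 right for a two-sided test, but the article specifies separate cross-sections.

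**There is no success rule.** The article lists many indicators, names no single primary endpoint, and plans estimates without a significance-based criterion. That softens the consequence, since misreading a null result is a risk and not a planned step. It does not make the stated power correct.

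**Two stronger readings are tempting.**
- A reader might take "We expect that 30% of the local population will seek care at a government facility" and dilute the 5 mmHg to 1.5 mmHg (0.30 × 5), with very low power. The 30% refers to the whole local population. The article gives no such figure for diagnosed hypertensives, who may use government facilities more, and it does not say that 5 mmHg is an effect among users only.
- A reader might infer that villages will be redrawn at endline, and that keeping the same ones would cancel village effects and restore power. The article says only that the procedure is repeated, which does not settle this. Even complete removal of between-village variance gives only 67%.

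**Conclusion.** The point holds. The stated 80% power for 5 mmHg belongs to a comparison at one time point. For the planned difference-in-difference it is about 61% two-sided (about 73% one-sided), with a detectable difference of about 6.2 mmHg at 80% power. The lower bound under the plan's own implied design effect is 42% and 8.0 mmHg.

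These figures assume SD 18.5, ICC 0.018, 20% diagnosed prevalence, 10% refusal, four independent samples, equal village sizes, no gain from covariates and a normal approximation. The factor of two between the contrast that was sized and the contrast to be analysed follows from the design and needs none of the numerical inputs. The article's figures support a power statement that is too favourable. They do not support the claim that the survey is uninformative.

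**What to change.** Restate the power paragraph for the difference-in-difference estimator. Give the variance formula, say whether alpha is one- or two-sided, and apply the design effect to the number of hypertensives per village. Recompute power and detectable difference with the SD, ICC and diagnosed prevalence from the baseline survey, which the Current status section says is complete; about 61% and 6.2 mmHg are what the planning values give. Any credit for covariate adjustment should rest on a stated share of variance explained.

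Report the community SBP difference-in-difference as an estimate with its confidence interval, read against the detectable difference, so that an inconclusive result is not taken as evidence of no effect.

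This costs text only, plus a less favourable power figure. Restoring 80% by sample size would be expensive. Planned from the start, it needs about 430 × 1.144 / (0.20 × 0.9), roughly 2,730 adults per block per round, against 1754. With baseline fixed at 276 effective hypertensives per block, solving 2 × 342.25 × (1/276 + 1/n) = (5/2.802)² gives about 970 effective hypertensives per block at endline.
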